### 4.4. Eligibility Criteria

#### **Inclusion Criteria:**

- Community-dwelling (not LTC) ≥65 years of age;
- Able to ambulate 25 metres with or without a walking aid;

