**FRAILTY REHABILITATION: A COMMUNITY-BASED INTERVENTION TO PROMOTE HEALTHY AGING**

- At high risk for mobility disability/functional limitations as assessed by the John Morley FRail scale (score of  $\geq 2$ );
- Medical clearance from referring clinician, or for self-referrals, medical clearance from family physician to safely participate in exercise and take oral nutritional supplements;
- Can arrange transportation to the YMCA up to 2 times per week;

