| Primary     | Physical Function
[Baseline and 4-months]                                       | Short Physical Performance Battery (SPPB)
400-m Walk Test [walking speed, m/s]                                                                                                                                                                                                                                                                                                                                                                                                                                                                                                                                                                                                                                                                                             |
| Secondary   | Functional Abilities
[Baseline and 4-months]                                    | Frailty : Fit-Frailty App
Fear of Falling : Icon Falls Efficacy Scale (ICON-FES)
Fitness : Modified Rating of Perceived Exertion (RPE) scale (post-400m walk test)
Strength : Grip strength with handgrip dynamometer [kg]
Cognition : Montreal Cognitive Assessment (MoCA)
Health-related quality of life : EQ-5D-5L
Life Space Mobility : Life Space Assessment
Activities of Daily Living : Katz ADL and Lawton IADL
Activity and Sleep Patterns : ActiGraph GT9X Link Accelerometer Data
Depression/Mood : Geriatric Depression Scale (GDS-SF)
Nutrition : Mini Nutritional Assessment and SCREEN-8
Functional Mobility : Timed Up and Go (TUG) Test |

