## FRAILITY REHABILITATION: A COMMUNITY-BASED INTERVENTION TO PROMOTE HEALTHY AGING

recently discharged from inpatient units. In our geriatric outpatient clinic study, the mean baseline score was 6.3. Assuming baseline scores of approximately 6, we aim to improve or maintain group exercise and socialization scores (and not decline over time as it did in the FIT Trial control group) and achieve at least a 1.5 between-group difference with the multi-modal arm. **Improving SPPB scores by 1.3-points is substantial clinical meaningful change [54] and bringing scores above 7 represents an important functional difference [InCHIANTI study, scores below 7 were strongly associated with mobility disability which limits independence in the community [58]].** **Sample size (SPPB):** Assuming at least a 1-point difference at 6-month follow-up (e.g. SPPB= 6.5 in group exercise versus 7.5 in multi-modal, SD=2 based on FIT trial and our own pilot data), with alpha 0.05 and power of 90%, and factoring in a drop-out rate of 20%, we will need a total sample size of N=324 (108 per arm). **Sample size (Frailty):** Assuming at least a 0.05-point difference at 6-month follow-up (e.g. Frailty score 0.25 in group exercise versus 0.20 in multi-modal, SD=0.09 based on our CaMos study data [3], with alpha 0.05 and power of 90%, and factoring in a drop-out rate of 20%, we will need a total sample N=195 (65 per arm). **To achieve the power to examine both outcomes, we will target a total cohort of 324.**

In addition to examining important scientific questions related to the effectiveness of frailty rehabilitation and functional capabilities of older adults living with frailty, this study will examine whether frailty rehabilitation is a sustainable community-based model that decreases healthcare utilization. Significant societal benefits could be achieved if hospitalization and institutionalization can be postponed or avoided. Furthermore, with limited access to geriatric services, examining other models for supporting primary care providers in managing frailty patients are imperative.

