**Table 3: Analysis Plan of Co-Primary Outcomes**

| Objectives                                                                                                                                                                                                               | Hypotheses                                                                       | Outcomes                                                                                                                   | Analysis                                |
|--------------------------------------------------------------------------------------------------------------------------------------------------------------------------------------------------------------------------|----------------------------------------------------------------------------------|----------------------------------------------------------------------------------------------------------------------------|-----------------------------------------|
| In community-dwelling older adults with frailty, does frailty rehabilitation (multi-modal and exercise only), compared with control (daily activity), improve physical function measured by physical performance? | Improved physical function with intervention; greatest effect in the multi-modal | SPPB (total score, sub-component scores) at 4-months
Sub-group:
Comparison b/w intervention groups; adherence | one-way ANOVA, post-hoc analysis
GEE |
| In community-dwelling older adults with frailty, does frailty rehabilitation (multi-modal and group exercise only), compared with control (daily activity), improve physical function measured by walking speed?  | Improved frailty status with intervention; greatest effect in the multi-modal    | 400m Walk Test (continuous) scores;
Sub-group:
Comparison b/w intervention groups; adherence                  | one-way ANOVA, post-hoc analysis
GEE |

**Economic analysis:** An individual-level economic evaluation alongside this trial will be done from the Ministry of Health perspective. We will examine changes in direct medical costs and effectiveness outcomes (e.g., quality-adjusted life years - QALYs), calculate and compare the ICER (e.g., \$/ QALY gained, \$/ a visit averted)[59] against a willingness-to-pay threshold (\$50,000/QALY)[60] to show if this program of frailty rehabilitation represents good value for money.

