|----------------------------------------------------------------------------------------------------------------------------------------------------------------------------------------------------------------------------------------------------------------------------------------------------------------------------------------------------------------------------------------------------------------------------------------------------------------------------------------------------------------------------------------------------------------------------------------------------------------------------------------------------------------------------------------------------------------------------------------------------------------------------------------------------------------------|----------------------------------------------------------------------------------------------------------------------------------------------------------------------------------------------------------------------------------------------------------------------------------------------------------------------------------------------|
| 
7) At risk for mobility/functional limitations as assessed by the John Morley FRAIL Scale. Has 2 or more of the following markers of frailty:
 
 
1. Difficulty climbing stairs, slow gait speed (e.g. have begun walking slower, or difficulty walking several hundred yards or about 2 kilometers)
 
2. Recent weight loss (unintentional)
 
3. Declines in energy (feel tired or fatigued often) and/or low physical activity
 
4. Previously diagnosed with 5 or more of the following illnesses: hypertension, diabetes, cancer, chronic lung disease, heart attack, congestive heart failure, angina, asthma, arthritis, stroke, kidney disease
 
 
*Frailty will be formally assessed at the study-screening visit
 | 
8) Terminally ill  NO  YES
 <hr/> 
9) Another household member enrolled in the study  NO  YES
 <hr/> 
10) Unable to attend for more than 20% of the trial duration  NO  YES
 |

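### The 400-m walk co-primary is a continuous speed compared by ANOVA, but the protocol defines no value for participants who cannot complete or attempt 400 m, although entry requires only 25 m

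*Protocol*

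**What the plan says.** Table 2 lists the second primary measure as "400-m Walk Test [walking speed, m/s", measured at baseline and 4 months. Table 3, titled "Analysis Plan of Co-Primary Outcomes", takes it as "400m Walk Test (continuous) scores" and assigns "one-way ANOVA, post-hoc analysis", with GEE listed beside it. Section 6.0 places the primary comparisons at 4 months, promises between-group differences with 95% confidence intervals, and states that all analysis follows intention to treat. Its sensitivity analyses are a cohort of trial completers and a GEE that examines covariates, including adherence.

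Four places bear on who will take the test:

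- Section 4.4 requires only "Able to ambulate 25 metres with or without a walking aid".
- Section 4.4 also selects people "At high risk for mobility disability/functional limitations as assessed by the John Morley FRail scale", with a score of at least 2.
- The referral form in Appendix A counts "difficulty walking several hundred yards or about 2 kilometers" within one of the qualifying markers.
- Section 5.0 assumes a baseline SPPB of about 6 and notes that "scores below 7 were strongly associated with mobility disability which limits independence in the community". By its title in the reference list, the study cited there concerns loss of the ability to walk 400 metres.

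No section says what is recorded for a participant who stops before 400 m or cannot start. Section 4.8, by contrast, gives SPPB a range of 0 to 12, so its lower end is defined.

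**The concern.** The trial recruits people partly for limited walking ability and then measures a co-primary outcome that exists, in its natural form, only for those who cover 400 m. That distance is 16 times the entry requirement (400 / 25). A one-way ANOVA uses only participants who have a value. Without a scoring rule, the simplest reading in practice is that a person with no 400-m speed does not enter the comparison.

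Completion at 4 months is itself something the intervention is meant to improve. If an effective arm brings more slow walkers to the finish, those walkers lower that arm's mean among finishers, while their counterparts in control are absent. The difference then shrinks, and the frailest participants, for whom the programme is designed, drop out of the estimate.

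How a non-completer scores is part of defining the outcome. It also decides what assessors must write down at the test, since distance and time at stopping cannot be recovered afterwards.

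**Working it through.** **The plan's own figure.** Section 5.0 sizes the trial on SPPB: difference 1, SD 2, alpha 0.05 (taken as two-sided), power 90%, dropout 20%. The normal formula 2(1.960 + 1.282)² × 2² / 1² gives 84.1, so 85 per arm; the t-test version gives 86. Then 86 / 0.8 = 107.5, so 108 per arm and 3 × 108 = 324. The stated size reproduces. It contains no allowance for 400-m non-completion, and no difference or SD is given for the 400-m walk.

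**Power if non-completers have no value.** Assume the SPPB standardised difference of 0.5 also applies to the 400-m walk, and that non-completion removes equal shares from each arm after dropout. Power = Φ(0.5·√(n/2) − 1.96).

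| Further share without a speed | Evaluable per arm | Power | Randomised per arm to keep 86 evaluable |
|---|---|---|---|
| 0% | 86 | 90.6% | 108 |
| 10% | 77 | 87.3% | 120 |
| 20% | 68 | 83.0% | 135 |
| 30% | 60 | 78.2% | 154 |
| 40% | 51 | 71.4% | 180 |

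The last column is 86 / (0.8 × (1 − share)), rounded up. The table counts lost numbers only and leaves the effect at 0.5.

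**Bias if finishers only are compared.** Let walking capacity be normal with SD 1, let treatment shift it by k SD, and let a participant finish when a completion score exceeds a cut c. The score has correlation ρ with speed, and treatment moves it by ρk. Set c so that a share q of controls do not finish. With λ(a) = φ(a) / (1 − Φ(a)),

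estimated / true = [k + ρλ(c − ρk) − ρλ(c)] / k.

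Worked case: q = 20%, ρ = 1, a true gain of 0.10 m/s and an SD of 0.25 m/s (both assumed), so k = 0.4. Then c = −0.842, λ(c) = 0.350 and λ(c − 0.4) = 0.207. The ratio is (0.4 + 0.207 − 0.350) / 0.4 = 0.64, so 0.10 m/s is estimated as about 0.064 m/s. Non-completion in the treated arm is 10.7% against 20% in control.

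Over the assumed ranges, the estimated difference as a fraction of the true one is:

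| Control non-completion | ρ = 0.5 (k 0.3–0.5) | ρ = 0.8 (k 0.3–0.5) | ρ = 1 (k 0.2–0.5) |
|---|---|---|---|
| 10% | 0.93–0.94 | 0.84–0.85 | 0.74–0.78 |
| 20% | 0.90 | 0.76–0.77 | 0.61–0.66 |
| 30% | 0.88 | 0.70–0.71 | 0.52–0.56 |
| 40% | 0.86 | 0.65–0.66 | 0.45–0.49 |

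For ρ = 1 the range of k covers gains of 0.05–0.10 m/s with an SD of 0.20–0.25 m/s. A simulation with one million participants per arm, for k of 0.3 and 0.5, agrees with the formula to within about 0.01. In this model the distortion always runs towards zero when treatment helps people finish.

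**The case against.** The strongest reply is that the protocol never excludes anyone. It records a speed, not a time to complete, and a speed could be computed from the distance covered or set to zero. The intention-to-treat statement points towards inclusion, and the scoring rule may stand in a statistical analysis plan or assessor manual that is not shown. This is right as far as it goes: exclusion is inferred from silence. A reader might infer that the plan discards non-completers and so contradicts its own intention-to-treat statement. The text does not support that. It leaves the value undefined, and the conflict arises only if such participants are left out.

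A reader might also infer that bias is certain. It is not. The primary comparison is at 4 months and an ANOVA on 4-month values needs no baseline walk. Inability that persists whatever the arm is balanced by randomisation; it narrows the population and costs power. Bias needs completion to depend on treatment.

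Nor do the documents establish that a large share will fail. The 25-m rule is a minimum, difficulty is not inability, and the SPPB statement is an association. The ρ = 1 column assumes that speed alone decides who finishes, whereas endurance, pain or refusal may also do so. It is the extreme of the range.

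What survives is that non-completion is foreseeable from the protocol's own text, and that the variable and the test are fixed without a value for those it affects. A speed from partial distance would not settle the matter, because it credits someone who stops early as if that pace had been held to the finish. Neither sensitivity analysis assigns a value to non-completers. SPPB, on which the sample size rests, is untouched.

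**Conclusion.** The point holds conditionally. The protocol defines no 400-m value for participants who cannot complete or attempt the test, in a trial whose entry rules make such participants likely. If they are left out of the ANOVA, the comparison is no longer intention to treat and power falls from about 91% to 87–71% for 10–40% non-completion. Where treatment helps people finish, the estimate is probably biased towards no difference, at about 0.45–0.94 of the true effect.

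These sizes rest on assumptions about the completion rate, the link between completion and speed, the SD and the gain. The documents give none of them. The power figures also borrow SPPB's standardised difference. The point is worth fixing before outcome data are seen, but it is not a defect that invalidates the trial.

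**What to change.** Amend Tables 2 and 3 as follows:

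- Include every randomised participant assessed at 4 months in the 400-m comparison, whether or not the walk is finished.
- Record distance and time at stopping.
- Give non-completers a defined value below all finishers, ordered by distance, with 0 m for those unable to start.
- Compare arms by a rank-based or ordinal analysis, either as the 400-m analysis itself or at least as a pre-specified sensitivity analysis. Ranking is one sound option among several; what matters is that the rule is fixed in advance.
- Report the proportion completing 400 m by arm, alongside mean speed in finishers.

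The cost is wording plus two entries from a test already being performed. The downside is that the all-participant result is not a simple mean difference in m/s, so the finisher mean must be labelled as supportive if the rank analysis becomes primary.

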## 7.0. TRIAL MANAGEMENT

The coordinating centre for the study is at the GERAS Centre for Aging Research at Hamilton Health Sciences. Overseen by the scientists and post-doctoral candidate, the research staff will be responsible for initiating the randomization procedure, submitting/maintaining REB documents, scheduling assessments, check-in phone-calls, receiving and storing consent forms. The study Steering Committee will meet every 6 months to provide overall supervision of the trial. The research assistant will call more frequent Steering Committee meetings if required. The **steering committee** will consist of: Dr. **[name]**, Director of Geriatric Medicine at McMaster with extensive experience in inter-professional education. Dr. **[name]**, a health economist and will oversee economic analysis. Dr. **[name]**, a geriatrician and international leader in frailty and dementia. Dr. **[name]** is a Gerokinesologist whose research is focused on aging, frailty, and their interaction with physical activity. Dr. **[name]** is a Family Physician and Director of Research for Family Medicine at McMaster and is the lead author of TAPER (TaperMD.com). Dr. **[name]** is a pharmacist and one of the founding leads of the 8.7 million dollar Health TAPESTRY primary care initiative. Dr. **[name]** is an international leader in osteoporosis, osteoarthritis, and sarcopenia. Dr. **[name]** is a biostatistician and international expert in trial methodology. Dr. **[name]** is a nurse researcher with expertise in qualitative analysis and public health/primary care collaboration. A **Data and Safety Monitoring Board (DSMB)** will oversee the study (bi-annual meetings), which can recommend changes to the protocol or termination of the study.

Upon request, the research staff will submit quarterly oral or written reports on study progress including but not limited to information on study subject enrollment, publication plans, and any adjustments in the estimated study completion date. Within 45 days following the completion or termination of the study, the

## **FRAILTY REHABILITATION: A COMMUNITY-BASED INTERVENTION TO PROMOTE HEALTHY AGING**

research staff will submit a final report detailing the results of the study to Abbott Nutrition and Abbott Nutrition representatives. The study reports shall be considered confidential information of McMaster University.

### **8.0. POTENTIAL RISK AND BENEFITS**

**Risks:** The potential risks of the study are reasonable. There may be a slightly greater risk of falling, musculoskeletal injury and/or fatigue with engaging in exercise classes and assessments of physical function/frailty. To minimize risks, participants will be cleared for exercise by their primary care physician or referring physician prior to beginning; classes will be tailored to meet the varied needs of frail older adults and administered by expert exercise trainers and the study physiotherapist. Further, the use of walking poles in-class, apart from its efficacy, is also due to the safety and stability it offers. At any time if participants feel uncomfortable, they may decline participation at any time.

For participants that are selected and have consented to wear an ActiGraph accelerometer, there is a small risk of a privacy breach for data collected on the external servers. ActiGraph complies with the Health Insurance Portability and Accountability Act of 1996 (“HIPAA”) and its amendments to ensure the protection of Protected Health Information (“PHI”). Safeguards that are currently used to ensure the protection of private health information include administrative procedures, physical data safeguards, electronic data access security, and network security that complies with legal requirements.

For participants who choose to provide an electronic signature via DocuSign, DocuSign is fully compliant with all data residency requirements and data privacy legislation governed federally under PIPEDA.

For potential participants who choose to self-refer to the Geras Centre website, the website has an AES-256 bank/military grade database storage encryption and has security measures in place to help prevent sensitive data breaches.

**Benefits:** If we can prove that frailty rehabilitation within our setting was effective, the next phase is to consider the generalizability of our approach, i.e., how this model could be applied within communities of varied size, demographic composition, geographical location. Our avoidance of specialized geriatric assessment teams allows for the potential for uptake in smaller centres and our partnership with the YMCA could help with pan-Canadian expansion. There are 120 Health & Fitness Centres across Canada serving 1.2 million Canadians of all ages. Further, the YMCA is a charitable organization that believes programs should be accessible to everyone regardless of age, background, ability or socio-economic status (e.g., fee assisted memberships are available). Our frailty rehabilitation model could be generalized to other community centres to increase the program accessibility.

### **9.0 ADVERSE EVENTS (AE)**

Participants will be instructed to contact the study coordinator if they experience any unfavorable/unintended signs or symptoms. Any untoward medical occurrence in a research participant, administered investigational product, including an occurrence which does not have a causal relationship with the product. An AE can be any unfavorable and unintended sign, symptom, or disease temporally associated with the use of an investigational product, or not related to the investigational product. Adverse events or harm in this study such as falls, fracture,

**FRAILTY REHABILITATION: A COMMUNITY-BASED INTERVENTION TO PROMOTE HEALTHY AGING**

pain with exercise, dizziness, chest pain, death or any other event from any source will be reported to the research team and recorded on a structured form. If applicable under the regulations governing the study, the research staff shall report adverse events that occur during the course of the study to Abbott Nutrition. The research staff shall also report all periodic reports regarding the study to Abbott Nutrition along with any safety issues related to the study or safety signal associated with the Abbott Nutrition study product.

**9.1 SERIOUS ADVERSE EVENTS (SAE)**

Any local serious adverse events that in the opinion of the local Principal Investigator is both unexpected and related or possibly related to, the study intervention or research procedures, must be reported to the REB.

If any adverse events meet the criteria for a serious adverse event such as a fatal, life threatening event resulting in significant or persistent disability/incapacity, requiring or prolonging hospitalization or presenting other significant hazards or potentially serious harm in the judgment of the site investigator will be reported to the Research Ethics Board within 7 business days of becoming aware of the event.

